#### Ethics considerations

The EMPA-CARD trial is conducting in accordance with the principles of the declaration of Helsinki and all subsequent revisions. The study was approved by the ethics committee of Zanjan university of Medical Sciences. All patients are provided with written informed consent by the investigators prior to the recruitment. Moreover, the study protocol was prospectively registered on the Iranian Registry of Clinical Trials (www.IRCT.ir, Identifier: IRCT20190412043247N2).

#### Trial population and eligibility assessment

Our goal is to randomize 100 participants from registries of 4 clinical centers (*i.e.,* Mousavi hospital (coronary angiography registry), Vali-e-Asr hospital, and two cardiology clinics of Zanjan University of Medical Sciences) in Zanjan, Iran. The pooled population of the clinics is 8000 patients, whose records were extracted from registries at the pre-recruitment phase. Patients aged between 45 and 75 years old with T2DM and known coronary artery disease (established by coronary angiography) who are on background standard anti-ischemic and anti-diabetic therapy with an HbA_1C_ between 6.5 and 9.5% were eligible for inclusion. The type and dose of background anti-diabetic medications should be constant for at least 3 months prior to recruitment. Patients’ left ventricular ejection fraction (LVEF) must be higher than 40%. Moreover, they must not be receiving anti-oxidant, anticoagulant, or antiplatelet medications or supplements (except for aspirin at 80 mg/d) for at least 3 months prior to recruitment. Detailed information for inclusion and exclusion criteria is provided in Table 2.

**Table 2 Tab2:** List of inclusion and exclusion criteria for randomization

Inclusion criteria	1. Age between 40 and 75 years 2. HbA1c between 6.5 and 9.5% 3. Documented known diabetes mellitus type 2 under continuous fixed-dose anti-diabetic treatment for at least 3 months prior to the randomization 4. Documented known coronary artery disease established by coronary angiography under continuous fixed-dose of anti-ischemic treatment for at least 3 months prior to the randomization 5. BMI less than 40 kg/m^2^ 6. Fixed diet and physical activity 7. eGFR greater than 45 ml/min/1.73m^2^ 8. Informed consent given in written form 9. Resting heart rate between 60 to 100 b/min
Exclusion criteria	1. Pregnancy 2. Heart Failure (NYHA class 3–4) 3. Left ventricular ejection fraction < 40% 4. Use of anti-coagulant or anti-platelet drugs (except aspirin 80 mg/daily) for at least 3 months prior to the blood sampling 5. Consumption of alcohol, continuous anti-inflammatory drugs (except aspirin 80 mg/daily) or anti-oxidant supplement 6. Use of pioglitazone 7. History of allergic reaction to SGLT2-i medications 8. History of SGLT2-i medication usage 9. Gastrointestinal malabsorption disease 10. History of CABG, ACS, TIA, CVA or PCI during past 3 month 11. History or presence of malignancy 12. Severe HTN Resting systolic blood pressure ≥ 180 mmHg and/or Resting diastolic blood pressure ≥ 120 mmHg 13. Anemia (Hb < 10 g/dl) 14. Platelet count < 100,000/µl 15. History of infection during 1 one month prior to blood sampling 16. History of heart or lung transplant 17. Major psychiatric disorders 18. History of DKA 19. Elevated liver enzymes > 3 times upper normal limit 20. Use of drugs which prolong QT interval 21. Presence of arrhythmia 22. Electrolyte imbalance 23. Patients with pace maker

*HbA*_*1c*_ glycated hemoglobin A_1c_, *BMI* body mass index, *eGFR* estimated glomerular filtration rate, *NYHA* New York Heart Association, *SGLT2-I* sodium-glucose co-transporter-2 inhibitor, *CABG* coronary artery bypass graft, *ACS* acute coronary syndrome, *TIA* transient ischemic attack, *CVA* cerebrovascular accident, *PCI* percutaneous coronary intervention, *HTN* hypertension, *Hb* hemoglobin, *DKA* diabetic ketoacidosis

#### Randomization and follow-up

The randomization method employed in this study is stratified randomization. During the screening process, eligible patients are stratified by gender (male and female), age (45–54, 55–64, and 65–75 years old), and HbA_1c_ (6.5–7.9% and 8–9.5%) and assigned into one of the two arms of the study (A or B). The randomization sequence is created using Winpepi software (version 11.6). The allocation sequence was concealed using the sealed envelopes mechanism. All participants will be followed up by phone calls every 4 weeks for assuring the proper medication usage, and for premature discontinuation or development of any adverse events. At the end of weeks 2, 12, and 26, patients are instructed to attend clinic visits for complete checkup and physical examination. Patients are also advised to return all used and unused medications at the end of week 26. The study’s follow-up and procedures are summarized in Table 3.

**Table 3 Tab3:**
[figure not shown]
SPIRIT flow diagram

*2D-TTE* 2-dimentional trans-thoracic echocardiography

*The safety measurements were done at the visit 0, visit 3 and whenever an adverse event occurs in a patient. The measurements included liver and renal function related laboratory measurements (aspartate-aminotransferase [AST], alanine-aminotransferase [ALT], alkaline phosphatase [ALP], creatinine [Cr] and blood urea nitrogen [BUN]), serum electrolyte measurements (sodium [Na], potassium [K]), coagulative measurements (prothrombin time [PT], partial thromboplastin time [PTT]), complete blood count (CBC), urine analysis (U/A), and urine culture (U/C) if the U/A become active and/or urogenital symptoms develop

#### Blinding

Empagliflozin and placebo tablets with the same color, shape, and package with the different code combination numbers are used for groups A and B. After enrollment, a code is assigned to each patient and will be used until the end of this study. Patients, researchers and healthcare providers who gather information and assess the outcomes and analyze the data of the study are blinded to the assigned treatment (empagliflozin or placebo) such that all patients will be evaluated under the unique assigned code and the treatment groups of A or B. In case of a need for un-blinding, the research council of Zanjan University of Medical Sciences will be notified by the chief investigator to discuss the terms of un-blinding. The un-blinded treatment list is held by the Zanjan University Medical Documentation Council which generated the allocation sequence and is not involved in the study. If the un-blinding is approved by the research council, the Documentation Council will be notified and ultimately the patient will be sent to an external clinical visit for further assessment and follow-up; meanwhile the chief investigator and research council will remain blinded.

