**Methods:**

In this multicenter, triple-blind randomized controlled trial, patients with documented known T2DM and CAD will be recruited. They will be randomized on a 1:1 ratio and assigned into two groups of empagliflozin 10 mg/daily and placebo. The primary endpoint is the effect of empagliflozin on changes of plasma interleukin 6 (IL-6) after 26 weeks of treatment. The secondary endpoints will consist of changes in other inflammatory biomarkers (Interleukin 1-beta and high-sensitive C-reactive protein), markers of oxidative stress, platelet function, and glycemic status.

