## Background

Diabetes mellitus (DM) is a chronic disease that is characterized by high blood glucose levels due to the inability to produce adequate amounts of insulin and/or resistance to the hormone’s actions [1]. Type 2 diabetes mellitus (T2DM) is a complex metabolic condition and, as the most common type of diabetes, it affects some 37% of the population in western and middle-eastern societies leading to long-term complications [2]. The major complications of this disease fall into two general categories of microvascular and macrovascular involvements, which can consequently lead to cardiovascular, neurological, ophthalmological, and renal damage [3]. Cardiovascular complications are the leading cause of death in the affected population. Atherosclerosis develops more rapidly in these patients and increases the incidence of a heart attack two to three times [4]. The management methods require multi-faceted strategies, including regular physical activity, proper diet, and medications to control hyperglycemia, hypertension, inflammation, and dyslipedemia [5, 6]. Among various medications available to treat diabetes, one of the newest ones is sodium-glucose co-transport 2 inhibitors (SGLT2-i) including empagliflozin, dapagliflozin, and canagliflozin. Empagliflozin is a selective inhibitor of the SGLT2 co-transporter expressed in the proximal tubule of nephrons. Inhibition of SGLT2 reduces hyperglycemia by decreasing glucose reabsorption in the kidneys leading to increased urinary glucose excretion, reductions in blood glucose and HbA_1C_ [7]. The EMPA-REG OUTCOME trial and its sub-studies revealed the additional beneficial effects of this medication versus standard treatment protocols in patients with T2DM and heart failure. These effects include a reduction in Major Adverse Cardiovascular Events (MACE), blood pressure, urinary albumin exertion, and improvements in lipid profile and vascular resistance [8, 9]. Some hypotheses have been advanced to explain the beneficial cardiovascular effects of this agent including hemodynamic changes due to decreased plasma volume following glycosuria-induced diuresis, changes in heart fuel consumption, improvements in overall metabolism by a reduction of inflammation, and direct effects on the cardiac tissue; however, the underlying mechanisms remain obscure [10, 11]. Many factors contribute to the physiopathology of cardiovascular complications in patients with T2DM including an increase in pro-inflammatory factors, imbalance in oxidative stress and a hyper-coagulation state with abnormal platelet function [12]. In this regard, animal models and in-vitro studies have been performed to evaluate the effects of empagliflozin on inflammatory state and platelet function. The results showed a reduction in oxidative stress, pro-inflammatory phenotype, and glucotoxicity, but platelet function remained unchanged [13, 14]. To date, few human model randomized trial has been performed to evaluate the inflammation and platelet dysfunction hypothesis in T2DM patients with coronary artery disease (CAD). Hence, the main objective of this parallel group, triple-blind randomized placebo-controlled trial is to test the hypothesis that empagliflozin improves the inflammatory state in T2DM patients with documented known CAD.

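### Outcome assessors work under a shared arm letter (A or B), so a few patients' urine results pooled by letter could disclose every allocation

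*Protocol article*

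**What the plan says.** The Blinding section of the protocol article states who is masked: "Patients, researchers and healthcare providers who gather information and assess the outcomes and analyze the data of the study are blinded". It then gives the mechanism: "all patients will be evaluated under the unique assigned code and the treatment groups of A or B". Tablets look alike, and packs "with the different code combination numbers are used for groups A and B". Randomization and follow-up also describes assignment in terms of arms A and B.

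Three other places bear on the point:

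- Background says that SGLT2 inhibition leads to "increased urinary glucose excretion".
- The Table 3 footnote lists safety tests at visit 0, visit 3 and whenever an adverse event occurs, among them "urine analysis (U/A), and urine culture (U/C) if the U/A become active" or if urogenital symptoms develop.
- Biobank says that stored plasma, serum and urine tubes carry the patient's own code. It mentions no arm letter.

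The only protection described for a disclosed treatment concerns formal un-blinding. The Documentation Council, which is outside the study, holds the list, the patient goes to an external visit, and the chief investigator and the research council stay blinded.

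**The concern.** Labelling a locked dataset A and B for a masked analyst is ordinary practice. The Blinding sentence goes further: it covers data gathering and outcome assessment as well as analysis, and it gives all three stages both labels.

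A two-level label shown to assessors ties all the patients' masks together. Anything learned about patients with one letter carries over to everyone else with that letter and, by elimination, to the other arm. The drug has a pharmacological marker that the planned safety tests can pick up.

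At stake are assessments that need human judgement: echocardiography, ECG reading (including ST-segment deviation), flow-cytometry gating for lymphocyte ROS and platelet CD62-P, and the physician's view of adverse-event severity and its consequences. If the letter is decoded, these can drift with treatment in every patient assessed afterwards.

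**Working it through.** The plan has no figure of its own to reproduce here beyond the planned size: "Our goal is to randomize 100 participants from registries of 4 clinical centers", which equals 2 × 50 from Sample size calculations. The Abstract gives the ratio: "They will be randomized on a 1:1 ratio and assigned into two groups of empagliflozin 10 mg/daily and placebo".

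**Step 1. What one decoded label discloses.** With patient-specific codes only, knowing one patient's treatment discloses that patient: 1 of 100. With two shared letters, knowing what A means also fixes B: 100 of 100.

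**Step 2. How strong one urinalysis is.** The documents give no glucose-positivity rates, so I assume s = 0.90 to 0.99 on empagliflozin and f = 0.10 to 0.50 on placebo. The placebo range is wide because patients with HbA1c up to 9.5% may have glucosuria without the drug. With a prior of 0.5 for each letter, the probability that a positive patient's letter is empagliflozin is

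0.5s / (0.5s + 0.5f) = s / (s + f).

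Low end: 0.90 / 1.40 = 0.643. High end: 0.99 / 1.09 = 0.908. This is suggestive, not conclusive.

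**Step 3. What the letter adds by pooling.** Let X and Y be the numbers positive among m patients on drug and m on placebo, with X ~ Bin(m, s) and Y ~ Bin(m, f). An observer names the letter with more positives as the drug and splits ties at random:

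P(correct) = P(X > Y) + 0.5 × P(X = Y).

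| s | f | One positive, s/(s+f) | m = 5 per letter | m = 10 per letter |
|---|---|---|---|---|
| 0.90 | 0.50 | 0.643 | 0.9241 | 0.9808 |
| 0.99 | 0.50 | 0.664 | 0.9795 | 0.9989 |
| 0.95 | 0.30 | 0.760 | 0.9932 | 0.9998 |
| 0.90 | 0.10 | 0.900 | 0.9991 | 1.0000 |
| 0.99 | 0.10 | 0.908 | 1.0000 | 1.0000 |

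(1.0000 means 1 to four decimals.) Without the shared letter this pooling is not possible.

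**Step 4. When it could happen.** Clinic visits after baseline are at weeks 2, 12 and 26, so visit 3 appears to be week 26. Current status puts the first randomization on 29 June 2020; adding 26 weeks (182 days) gives 28 December 2020. Routine on-treatment urinalyses therefore start about then, while adverse-event urinalyses could come sooner. By 9 November 2020, 91 patients were randomized, leaving 100 − 91 = 9. Decoding from routine results would thus bear on week-26 assessments of patients enrolled later, and hardly on who is allocated to what.

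**The case against.** The strongest reply is that one compressed sentence covers three activities and two labels. It could mean the individual code for assessment and A/B for masked analysis, with details in the trial procedure manual, which is not shown. That reading is possible, but the sentence does not make the distinction and no other section confines the letter to the analysis. The Biobank text helps the reply only for stored samples.

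A second reply is that if urine glucose is informative, each patient is partly recognisable under any code. That stands. Removing the letter prevents pooling and trial-wide disclosure, but not recognition of one patient from that patient's own result. The remedy therefore needs both parts.

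A third is that the consequence is limited. This also stands in large part. The only confirmatory outcome is IL-6 by ELISA; secondary outcomes are declared exploratory, and echocardiography and ECG belong to sub-studies.

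A reader might also infer four stronger things that the documents do not support:

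- That one glucose-positive urinalysis settles what A means. It does not (step 2), and the documents give no rate from which recognition could be called nearly certain.
- That one approved un-blinding exposes the trial. The Blinding section routes that patient to an external visit, keeps the chief investigator and council blinded, and does not say that the result returns to assessors.
- That sample tubes carry the letter. Biobank describes the patient's dedicated code.
- That remaining allocations become guessable. No block scheme is stated, envelopes are sealed, and at most nine allocations were outstanding well before the first routine week-26 result.

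**Conclusion.** The point holds as a weakness in the stated blinding mechanism that should be corrected. On its plain wording, the article shows data collectors and outcome assessors a shared arm letter that they do not need, and it withholds no urine results from them.

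The size is structural: decoding the letter discloses 100 of 100 allocations rather than 1 of 100. Five patients per letter would identify the drug letter with probability of about 92–100%, and ten with about 98–100%. These probabilities rest on my assumed positivity rates and on the same person, or people who confer, seeing both the letter and the urine results. With four centers and separate laboratories that may not always be so.

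The exposure is to reader-dependent exploratory and sub-study outcomes and to adverse-event judgement, in patients assessed after decoding. The primary IL-6 comparison is less exposed, and nothing here shows that the blind has been broken.

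**What to change.** State in the protocol and the procedure manual that:

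1. Data collectors and outcome assessors work under the unique patient code only, as the stored biobank samples already do. The letter does not appear on forms, image files or reading worksheets.
2. The Documentation Council, which already holds the list, releases masked A/B labels to the analyst only after database lock.
3. Post-baseline urine glucose results go to the safety physician and not to outcome assessors. That physician should likewise work without the letter, so that results cannot be pooled by arm.

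If assessors already work without the letter, it is enough to reword the Blinding sentence to say so and to add item 3.

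The cost is a small mid-trial change in record handling, with some care needed for the patients already randomized. Packs already coded by group need not be relabelled, provided that assessors do not see them. No extra visits or measurements are needed.

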### Outcomes

To assess the outcomes of the study and sub-studies, patients undergo blood sampling, electrocardiography (ECG), and 2D trans-thoracic echocardiography (Table 3).

#### Primary outcome

The primary outcome of this study is the changes in plasma interleukin 6 levels after 26 weeks of the treatment between the two study arms.

#### Secondary outcomes for the primary objective

The secondary outcomes for testing the hypothesis of the study’s primary objective are categorized into 4 divisions including (1) Changes in additional plasma inflammatory biomarker levels (high-sensitive C-reactive protein (hs-CRP) and plasma interleukin 1-beta (IL-1b)); (2) Changes in oxidative stress status (lymphocytic reactive oxygen species levels (ROS), plasma levels of malondialdehyde (MDA), carbonyl level, total antioxidant capacity (T-AOC), reduced glutathione level (GSHr), catalase enzyme (CAT) activity, and superoxide dismutase enzyme (SOD) activity); (3) Changes in platelet function (CD62-P expression on the platelet surface); and 4) Changes in glycemic status (Fasting Blood Glucose (FBS), HbA_1C_, and Homeostatic Model Assessment for Insulin Resistance (HOMA-IR)).

#### Additional secondary outcomes

The additional secondary outcomes will be considered for the EMPA-CARD sub-studies including (1) Changes in cardiac biomarkers (Serum high-sensitive troponin I (hs-Troponin-I), brain natriuretic peptide (BNP) and N-terminal pro-brain natriuretic peptide (NT-proBNP) levels); (2) Changes in Echocardiographic parameters (left ventricular systolic and diastolic function and right ventricular function); (3) Changes in hematopoietic status and renal function (blood hematocrit, hemoglobin, and serum erythropoietin, and urine microalbuminuria levels); (4) Changes in lipid profile (serum total cholesterol, Low-Density Lipoprotein (LDL) cholesterol, High-Density Lipoprotein (HDL) cholesterol, and triglyceride levels); and (5) Changes in electrocardiographic parameters (PR interval duration, QRS complex duration, QT interval duration, ST-segment deviation, and T wave alternans).

All the above secondary outcomes will be assessed as the changes from baseline to week 26 of treatment in each study arm. Measurements of the biomarkers will be performed in the biotechnology laboratory of the Zanjan University of Medical Sciences and the Mousavi Hospital’s laboratory. The detailed information about the mentioned outcomes is presented in Table 4.

**Table 4 Tab4:** The detailed descriptions of selected outcomes

Outcome	Method of measurement	Mechanism	Time of measurement
Changes in plasma IL-6 and 1-beta levels	Plasma IL-6 and IL-1b Elisa kits	Key cytokines in development and maintenance of inflammation	Week 0 and 26
Changes in oxidative stress (Lymphocytic ROS, plasma MDA, Carbonyl, T-AOC, GSHr, CAT activity and SOD enzyme activity levels)	Flow cytometry (DCFDA as dye)^a^, spectrophotometry, colorimetric and FRAP assays	ROS, MDA and carbonyl increase in inflammation and causes cell damage GSHr, AOC, CAT activity and SOD activity increase in inflammation and reduce oxidative stress	Week 0 and 26
Changes in serum hs-CRP level	Turbidimetric assay	Circulating concentrations rise in response to inflammation	Week 0 and 26
Changes in platelet function^b^	Flow cytometry (MFI of CD62-P expression on platelet surface)	Platelet activity increases in DM and inflammation causing platelet dysfunction	Week 0 and 26
Changes in HbA_1c_, FBS and Basal Insulin level	Enzymatic assay	Indicate the glycemic status which is reduce with anti-glycemic drugs	Week 0 and 26
Changes in HOMA-IR^c^	fasting insulin (mU/mL) × fasting glucose (mg/dL)/405	A method used to quantify insulin resistance which increases in DM and insulin resistance conditions	Week 0 and 26
Changes in serum hs-troponin I, BNP and NT-proBNP levels	Chemiluminescence assay	Specific cardiac biomarkers increase in cardiomyocyte damage and tension	Week 0 and 26
Changes in blood Hb, Hct and serum erythropoietin	CBC and serum erythropoietin Elisa kit	Reflects the hematopoietic status	Week 0 and 26
Changes in urine micro-albuminuria and albumin to creatinine ratio	Photometry and enzymatic assays	Reflects the renal and glomerular function. May increase in in DM as a microvascular adverse event	Week 0 and 26
Changes in lipid profile (serum TG, cholesterol, HDL,LDL cholesterols)	Enzymatic assay	Lipid disorders increase in DM which raises the cardiovascular complications that may decrease with empagliflozin treatment	Week 0 and 26
Changes in echocardiography parameters	2D trans-thoracic Echocardiography	Reflects left ventricular systolic and diastolic and right ventricular function	Week 0 and 26
Changes in electrocardiographic parameters	Electrocardiography	Reflects the electrophysiological activity of the heart	Week 0 and 26

*IL-6* interleukin 6, *IL-1b* interleukin 1-beta, *ROS* reactive oxygen species, *MDA* malondialdehyde, *T-AOC* total antioxidant capacity, *GSHr* reduced glutathione, *CAT* catalase, *SOD* superoxide dismutase, *DCFDA* dichlorofluorescin diacetate, *FRAP* fluorescence recovery after photobleaching, *hs-CRP* high sensitive C-reactive protein, *MFI* mean fluorescent index, *DM* diabetes mellitus, *HbA*_*1c*_ glycated hemoglobin, *FBS* fasting blood glucose, *HOMA-IR* homeostatic model assessment for insulin resistance, *hs-Troponin I* high sensitive troponin I, *BNP* brain natriuretic peptide, *NT-proBNP* N-terminal pro-brain natriuretic peptide, *Hb* hemoglobin, *Hct* hematocrit, *CBC* complete blood count, *TG* triglyceride, *HDL* high density lipoprotein, *LDL* low density lipoprotein cholesterol

^a^To assess the changes in ROS production, peripheral blood mononuclear cells (PBMC) will be separated from fresh whole blood and lymphocytes will be gated through sample acquisition in flow cytometric analysis

^b^To minimize the time interval between sample drawing and sample acquisition (less than 90 min) and any further manipulation which may result in unwanted platelet activation, the activation test was set up on whole blood via Thrombin Receptor Activator Peptide 6 (TRAP-6). The platelet concentrated area will be gated during sample acquisition and the MFI in histogram plot will be measured by Human CD62-P FITC antibody

^c^Patients who are under treatment with insulin in any form will be excluded from the analysis

